#### Secondary objective (prognostic models)

A key secondary objective is to develop prognostic models (ie, risk scores or risk calculators) that estimate a cirrhosis patient’s individualised risk of developing HCC in the future. The investigators will approach this in two main ways. First, developing static risk models that incorporate biomarker data collected at a single time point only (ie, study enrolment). Second, building dynamic models that leverage the serial data collected for Pearl participants to estimate individualised HCC risk. As with our primary outcome, our focus will be on developing models that combine multiple prognostic factors/detection assays.

In general, we will endeavour to align all statistical analyses with ‘best practice’ guidelines established in the TRIPOD (Transparent Reporting of a multivariable prediction model for Individual Prognosis or Diagnosis) statement.^32^

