## Abstract

**Introduction:**

Hepatocellular carcinoma (HCC) is the fastest-rising and fourth most common cause of cancer death worldwide. Liver cirrhosis is the largest underlying risk factor for HCC. Therefore, patients with cirrhosis should have regular ultrasound and biochemical screening to pick up early HCC. Early HCC can be cured; more advanced HCCs have limited treatment options and poor prognosis. Current screening methods are suboptimal with poor sensitivity in picking up early disease. In this study, the investigators aim to recruit people with liver cirrhosis into a Prospective cohort for early detection of liver cancer—the Pearl cohort. The investigators believe that by using state-of-the-art tests we can improve the detection of early HCC.

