## Methods and analysis

### Study design

Pearl will be a UK-based prospective, longitudinal, diagnostic and prognostic, multicentre study. This study is observational in nature and does not require any interventions (ie non-CTIMP (clinical trial of investigational medical product) or changes to standard clinical care.

The investigators aim to enrol 3000 participants from specialist liver clinics from multiple NHS hospital trusts in the UK. These trusts will be those that are part of the National Institute for Health Research Clinical Research Network (NIHR CRN) and NHS Research Scotland. Participants will have a diagnosis of liver cirrhosis and no history of HCC. All will be attending specialist services for management and treatment of their disease and routine screening for HCC. Enrolled participants will be asked to complete at least three visits; a baseline visit plus two further follow-up visits over a period of 3 years. An unscheduled visit may occur if a participant is diagnosed with HCC. During each study visit, participants will have samples taken and clinical data and information collected. Wherever possible, these study visits will be timed to coincide with routine clinic visits to minimise the burden for participants in terms of travel to the hospital, time spent in clinics, additional blood tests and other assessments.

Long-term follow-up of medical records from national health registries will be conducted for at least 10 years after the end of the active follow-up phase. Data obtained from NHS England and other patient registries will include decompensation episodes, HCC diagnosis, liver transplantation and death (see figure 2).

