### Exclusion criteria

Diagnosis of current or historical HCC.Liver transplant recipients or patients on active listing for liver transplantation.Child-Pugh C cirrhosis.In the view of the clinician, if the patient has a comorbidity likely to lead to death within the following 12 months.In the view of the clinician, if the patient is not thought to be suitable for HCC surveillance.

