### Protocol procedures

Each participant will have three scheduled study visits: one baseline visit and two subsequent follow-up visits over a 3-year period. During the baseline visit, participants will be consented, enrolled into the study and allocated a unique study number. Their demographics, anthropological measurements (height, weight and body mass index), medical history and previous clinical imaging data will be collected. They will also have blood and urine samples collected and stored. All data and biological samples will be recorded against their unique study number.

During the two subsequent scheduled follow-up visits, 18 months after previous visits (which will be timed to coincide with routine clinic appointments where possible) there will be further collection of data as above (including blood and urine samples). If participants are unable to attend a face-to-face appointment the participant may be contacted via phone or email to respond verbally or online to a questionnaire (for medical history and demographic data).

Participants may have unscheduled follow-up visits. This will occur if the participant is diagnosed with HCC and should happen as close as possible to the date of HCC diagnosis. Participants will have the same data points, including blood and urine samples collected on this visit. Blood and urine samples will need to be collected prior to initiation of any treatment for HCC. Follow-up will then continue as per the standard protocol to ensure outcome data and samples are collected (see figure 2).

If the participant received a liver transplant, they would remain part of the study but no further follow-up visits or samples are required. If the participant dies the cause of death will be recorded clearly.

Beyond the 3-year active follow-up process, NHS England data from participants will be obtained for at least 10 years after the last participant contact. This passive follow-up will involve no direct participant contact.

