### Sample handling and analysis

Participants will have blood and urine samples taken on each study visit (both scheduled and unscheduled). The research samples will be collected, have initial processing in the local laboratory and stored (as per sample collection protocol) prior to transfer to Oxford University labs.

Samples are handled and stored as per Human Tissue Act requirements; all samples are labelled with a unique visit ID and will not contain any personally identifiable information. All future subdivisions of the sample will be allocated a new unique barcode. Linking of clinical data to the samples will be possible using unique participant study numbers and visit ID numbers.

The blood samples will be tested for state-of-the-art biomarkers including (but not limited to):

Detection of epigenetic and genetic mutations and copy number variations in circulating tumour DNA.Polygenic risk scores derived from germline genetic sequencing.Detection of autoantibodies to tumour-associated antigens.Protein biomarkers include the L3 isoform of AFP and des-gamma-carboxyprothrombin.Viral sequencing (HBV and HCV).Proteomics and metabolomics.

The urine samples will be analysed for:

Proteomic and metabolomic profiling including steroid metabolic signatures in urine.

Analyses will be carried out in laboratories within the University of Oxford or with collaborators at other academic institutions. Participant consent for these analyses and storage and future use of remaining blood and urine samples for yet unspecified ethically approved research purposes will be sought. Samples will be retained indefinitely.

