**Figure 3 F3:**
[figure not shown]
Schematic outlining how the Pearl cohort will be used in conjunction with the SELiNa cohort. HCC, hepatocellular carcinoma.

A key secondary objective of Pearl is to develop prognostic models for ‘risk-stratifying’ patients with cirrhosis according to their future risk of HCC. This could enable clinicians to personalise HCC surveillance. The models developed will be evaluated primarily in terms of their discriminative ability (ie, ability to differentiate individuals who develop HCC from those who do not), measured via the Concordance Index (C-Index). In this context, the C-index will indicate the degree to which individuals who develop HCC have a higher risk score than those who do not.

An additional secondary objective includes quantifying the cumulative incidence of HCC among people with cirrhosis and determining how this varies by underlying cirrhosis aetiology in a UK setting. The cumulative incidence of HCC (stratified by HCC aetiology) will be measured at 1, 3 and 5 years postbaseline.

A further secondary objective will be using the Pearl cohort to identify patients at high risk of developing HCC using the AMAP clinical risk score, for the development of novel MR imaging as part of the separate AMULET study.^31^

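### With no gap between the enrolment sample and the counting of HCC, the C-index of the static prognostic models will in part reflect detection of tumours already present

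*Protocol article*

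**What the plan says.** **Aim and metric.** Under Objectives and outcome measures, a key secondary objective is to stratify patients with cirrhosis "according to their future risk of HCC". The models are judged mainly by the C-index and are meant to help tailor surveillance.

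**Predictors.** The section on prognostic models plans "developing static risk models that incorporate biomarker data collected at a single time point only (ie, study enrolment", followed by dynamic models that use the serial samples. It adds that "our focus will be on developing models that combine multiple prognostic factors/detection assays". The assays listed under Sample handling and analysis include "Detection of epigenetic and genetic mutations and copy number variations in circulating tumour DNA", autoantibodies to tumour antigens, AFP-L3 and des-gamma-carboxyprothrombin.

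**Entry.** Existing cancer is excluded through "Diagnosis of current or historical HCC". At baseline, "medical history and previous clinical imaging data will be collected" (Protocol procedures), but no study scan and no maximum age of the last scan is stated. Study design says that "This study is observational in nature and does not require any interventions". The Abstract says of the tests that would have ruled HCC out: "Current screening methods are suboptimal with poor sensitivity in picking up early disease".

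**Counting.** Cumulative incidence is taken at 1, 3 and 5 years from baseline. Sample size expects about 90–180 cases over 5 years and derives 10–20 model parameters from them. The caption of Figure 4 indexes the expected cases by time since enrolment. The Abstract describes the 75 or so cases at 3 years as de novo. No lag or landmark is stated. The strengths and limitations box concedes that the time from sample to cancer varies, but no analysis step follows from this.

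**The concern.** The programme rests on the premise that better assays find tumours that routine screening misses. If that is so, some participants carry an undetected tumour at enrolment. Their baseline sample may be positive because the tumour is there, and the later diagnosis then counts as a successful prediction.

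The C-index cannot tell the two situations apart. It is inflated wherever an assay separates existing tumours from no tumour better than it separates future cases from non-cases, which is what one expects of a detection assay. A model helped in this way would perform less well in patients whose liver has just been shown to be clear. Those are the patients for whom a long-range risk score would set surveillance intensity.

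**Working it through.** **Inputs from the document.** 3000 recruited with 10% drop-out, giving 2700 (Sample size); all-cause mortality 5% per year (caption of Figure 4); about 75 cases at 3 years (Abstract); 90–180 cases at 5 years and 10 events per variable (Sample size); a standard screening interval of 6 months (Introduction).

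**Assumptions.** Figure 4 is not available, so the HCC rates are back-solved from the stated counts. Undiagnosed prevalence at entry and assay accuracy are not given in the document.

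**1. Reproducing the stated counts with no lag.** Annual life table: cases = sum over years k of 2700 × rate × 0.95^(k−1).
- 1%/year, 3 years: 27 × (1 + 0.95 + 0.9025) = 77.0 (stated: about 75).
- 0.75%/year and 1.5%/year, 5 years: 91.6 and 183.2 (stated: about 90–180).

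The planned counts are reached by counting every case from enrolment.

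**2. Share diagnosed early.** Continuous form: cases by time t = 2700 × h/(h+m) × (1 − exp(−(h+m)t)), with m = −ln 0.95 and h = 0.01.

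| Time from enrolment | Cases | Share of 3-year cases | Share of 5-year cases |
|---|---|---|---|
| 6 months | 13.3 | 18% | 11% |
| 12 months | 26.2 | 35% | 23% |
| 3 years | 74.0 | – | – |
| 5 years | 116.3 | – | – |

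These are shares diagnosed early under a constant rate. They are not estimates of how many tumours existed at baseline.

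**3. Effect on the C-index (illustration).** Let q be the share of cases already present at the baseline sample, and let the marker have no prognostic value, so its true C is 0.50. The C-index is treated as a case versus non-case comparison, as the article describes it.

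*Binary marker:* C = 0.5 + q × (sensitivity − (1 − specificity))/2, with assumed specificity 90% and sensitivity 50–70% for an existing tumour.
- q = 17%: 0.5 + 0.17 × 0.4/2 = 0.53, to 0.5 + 0.17 × 0.6/2 = 0.55.
- q = 33%: 0.5 + 0.33 × 0.4/2 = 0.57, to 0.5 + 0.33 × 0.6/2 = 0.60.

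*Stronger assumption, AUC 0.90 for existing tumours:* C = 0.90q + 0.50(1 − q).
- q = 11%: 0.54.
- q = 18%: 0.57.
- q = 36%: 0.64. This q comes from an assumed 1% undiagnosed prevalence, 27 of 75 cases. If the 27 are added to 74 incident cases instead, q = 27/101 = 27% and C = 0.61.

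**4. Cost of a landmark at 5 years.** Rates are solved to give exactly 90 and 180 cases (h = 0.0077 and 0.0157).

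| Landmark | Cases removed | Cases left | Parameters at 10 events each |
|---|---|---|---|
| None | 0 | 90–180 | about 9–18 (the article says about 10–20) |
| 6 months | 10.2–20.8 | 80–159 | about 8–16 |
| 12 months | 20.2–41.0 | 70–139 | about 7–14 |

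**The case against.** **The analysis plan may handle it.** The choice of landmark often sits in an analysis plan, which is not shown, and a target of future HCC is compatible with one. An unseen plan could indeed add it. But this article already states the predictors, their time point and an event budget that reproduces only without a gap. Adding a landmark would change that budget, and the general commitment to TRIPOD does not supply one.

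**The cohort is under surveillance.** Participants attend routine HCC screening, those unsuitable for surveillance are excluded, and earlier imaging is collected. This limits the number of undetected tumours. It does not remove them, given how the article itself rates the screening tests.

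**The effect dilutes with time.** On the 5-year horizon of the sample-size section, the first 6 months hold about 11% of cases, not 18%. Over 13 years (3 active plus 10 passive), the formula above gives about 242 cases, so 13.3/242 is about 5%. This stands, and the effect is larger for models fitted on the 3-year data.

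**Stronger readings do not hold.**
- A reader might infer that tumour markers will look prognostic solely because they detect existing tumours, or that most early cases were present at entry. The article gives no prevalence or accuracy figure to support either.
- A reader might infer that the diagnostic and prognostic objectives use the same samples. Protocol procedures provides for a separate pre-treatment sample at HCC diagnosis, and the article does not say which sample enters the diagnostic analysis.
- A reader might infer that counting from baseline is wrong in itself. Cumulative incidence from enrolment is a legitimate quantity, and a day-0 model is defensible for patients under surveillance, who also carry undetected tumours. A landmark answers a different question, which is why both analyses should be reported.

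**Conclusion.** The point holds in a limited form. Exclusion by diagnosis only, detection assays as enrolment predictors and events counted from enrolment together let detection of existing tumours contribute to a C-index that is meant to measure prediction.

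The direction is clear for detection assays; the size is not known. About 13 cases in the first 6 months (18% of 3-year and about 11% of 5-year cases) rests on an assumed constant rate of about 1% per year, and only some of those tumours will have been present at baseline. The apparent C-index of 0.53–0.60 for a marker with no prognostic value, or up to 0.64, rests on assumed accuracy and prevalence.

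The diagnostic primary objective is not affected by this point. It is a cheap improvement to a key secondary analysis.

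**What to change.** - **Prognostic models.** Prespecify a landmark analysis: count HCC diagnosed more than, say, 6 months after the predictor sample, with 12 months as a sensitivity analysis. Report it beside the day-0 analysis.
- **Dynamic models.** Apply the same gap after each later sample.
- **Early cases.** Report HCC diagnosed before the landmark separately.
- **Cumulative incidence.** Keep it from baseline, but show the first 6 months separately and do not describe those cases as de novo.
- **Event budget.** Restate it: at 5 years a 6-month landmark supports about 8–16 parameters and a 12-month one about 7–14, against the stated 10–20.

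The change needs wording and programming only, with no new visits, samples or recruitment. Its price is the lost events. One screening round also reduces the share of tumours already present without eliminating it, which the report should say.

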### Sample size

The study will aim to recruit 3000 patients with cirrhosis over 30 months of specified aetiologies. There is an expected ~10% drop-out rate, leaving a final cohort size of 2700. There are currently more than 60 000 people living with cirrhosis^9^ and many of the recruiting centres have several hundred patients under annual surveillance. The study has received 23 letters of support from these centres which demonstrate the national interest in this study and demonstrate that the recruitment target is realistic. It is anticipated that this cohort will yield ~90–180 incident HCC cases over, for example, a 5-year time frame, depending on the HCC incidence rate observed (figure 4). Based on the rule-of-thumb of 10 events per variable, this would provide scope to include ~10–20 prediction parameters in our model, for this time horizon. Many of the parameters to be evaluated as part of the model will be selected depending on data generated from exploratory laboratory assays. The study has been adopted onto the NIHR CRN portfolio facilitating national recruitment.

**Figure 4 F4:**
[figure not shown]
Number of patients expected to develop HCC in the Pearl cohort, according to time since enrolment and HCC incidence rate (N.B. These estimates assume an overall sample size of 3000 patients with 10% attrition. All-cause mortality is estimated at 5% per year). HCC, hepatocellular carcinoma.

### Data handling

All study data will be entered into an Electronic Data Capture (EDC) system called REDCap or onto a paper source document for later entry into EDC if direct entry is not available. REDCap is a well-supported EDC that is widely used within the University of Oxford and further afield. It has been previously implemented in large national and international trials. The REDCap database is a secure database, fully compliant with Good Clinical Practice (GCP), European Union and UK regulations, allows a full audit trail for tracking data manipulation and user activity and is backed up on a frequent basis. The database resides on secure firewalled servers maintained by the University of Oxford and located within the University of Oxford Medical Sciences Division secure network. Only members of the study teams have access to REDCap via individual username and password which only allows access to their specific data. Additional information may be recorded on a separate paper source document or electronic files.

The participants will be identified by a unique study-specific number in any database and other electronic or paper documents apart from the code break document (site enrolment log) and consent forms which will be stored securely in confidential conditions. With participant permission, we will store names, telephone numbers and email addresses for the purpose of facilitating telephone and/or email follow-up visits. Paper documents containing personal information will be stored in locked cupboards at study sites and access will only be given to the authorised persons. Electronic documents containing personal information will be stored on secure servers with access restricted to the local study team in the case of the enrolment log or the Pearl Management Group which can access participant contact details.

Personal information such as contact details will be destroyed no later than 12 months after the end of the study unless the participant has agreed to be contacted for future research in which case the personal information will be transferred to another secure database. The personal identifiers (name of participant) contained in consent forms will be stored or accessed for up to 5 years after study end by the study sites, after which time the custodian will agree on a date for destruction and it will be destroyed confidentially. Fully anonymised research data obtained from assays and analysis will be stored and accessed indefinitely for the purpose of continuous publication opportunities. To facilitate long-term data collection of mortality and cancer-related endpoints, study investigators may request patient information from NHS England and/or other patient registries. Of note, the NHS and CHI numbers of participants will be recorded in REDCap for the purpose of linkage with patient registries. Data returned to the research team will only contain the unique study-specific number.

## Ethics and dissemination

Pearl will be conducted in accordance with the principles of the Declaration of Helsinki, relevant regulations and GCP guidelines.

Approval for the study has been obtained from HRA and REC. The study has been registered on ClinicalTrials.gov (NCT05541601). As a non-CTIMP, observational study, there will be minimal risks associated with participation. The risks involved would be those of venepuncture.

This protocol is version 3.0 (30 June 2023): there have been two substantial amendments to the protocol which have both received HRA and HCRW approval.

The results of the study will be published in a peer-reviewed journal and presented at relevant conferences.

### Patient and public involvement

Input into the study design as well as the generation of protocol and participant information sheet has been sought from patient groups (as part of the British Liver Trust and the Hepatitis C Trust) and patient representatives are part of the DeLIVER programme Management and Steering Committee which will discuss the management of all studies under the umbrella of the DeLIVER consortium, including the Pearl study.
